#### Missing Data

Each study initially uses a complete-case model, whereby individuals with missing observations are excluded from the model. Member Studies with missing exposure, outcome, and covariate observations conduct a missing data analysis to determine the influence of missing data. While a multiple imputation approach is preferred, other methods such as k-nearest neighbor imputation or inverse probability weighting may be used where an imputation approach is not possible or appropriate [36-41].

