Ultra-processed foods (optional)	Any intake of ultraprocessed foods, as defined by the Nova system as any food item in Nova category 4 (“ultraprocessed food”), in grams [20].	grams/day

^a^Based on the GBD (Global Burden of Diseases, Injuries, and Risk Factors Study) risk exposure definitions (Pages 217-218 in Supplementary Appendix 1 in the study by the the GBD 2019 Risk Factors Collaborators [19]).

^b^GBD: Global Burden of Diseases, Injuries, and Risk Factors Study.

^c^Analyses using continuous exposures are required by the GLAD Taskforce. The units listed here are recommended, however, these may be rescaled to more meaningful units in papers (eg, per 10 g) provided the original units are available to the project team.

**Table 2 table2:** Mental health definitions and recommended coding for the GLAD^a^ project^b^.

Mental disorder	Outcome definition	Diagnostic reference	Recommended coding^c^
Major depressive disorder	Involves the presence of at least one major depressive episode, which is the experience of either depressed mood or loss of interest/pleasure, for most of every day, for at least two weeks.	DSM-IV-TR^d^: 296.21–24; 296.31–34. ICD-10^e^: F32.0-9; F33.0-9.	0=no MDD^f^; 1= MDD
Anxiety disorders (any subtype)	Involves experiences of intense fear and distress, typically in combination with other physiological symptoms. Anxiety disorders will be modeled as a single cause for “any” anxiety disorder to avoid the double-counting of individuals meeting criteria for more than one anxiety disorder. Epidemiological estimates reporting an outcome for “any” or “total” anxiety disorders will be included if they reported on at least three anxiety disorders.	DSM-IV-TR: 300.0-300.3; 208.3; 309.21; 309.81. ICD-10: F40-42; F43.0; F43.1; F93.0-93.2; F93.8.	0=no anxiety disorder; 1=anxiety disorder

^a^GLAD: Global burden of disease Lifestyle And mental Disorders.

^b^The definitions and diagnostic references presented in this table are the current definitions used by the GBD (Page 4 in the Supplementary Appendix in the study by the GBD 2019 Mental Disorders Collaborators [1]). Since GLAD members may use alternative methods to ascertain disorder status, definitions or diagnostic references may vary slightly. For example, somatic forms of depression may be captured more by symptom scales, or studies using prescriptions may use Anatomical Therapeutic Chemical codes to determine incident depression and anxiety.

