#### Estimating Risk Ratios, Odds Ratios, and Hazards Ratios

Each study is required to use risk ratios (estimated by Poisson regression with robust SE) as the primary means of assessing the association of dietary intake with CMDs. Risk ratios are based on incident cases, and so models will need to exclude participants with depression or anxiety at baseline. Furthermore, to determine incident risk, studies must have dietary exposures at baseline and depression, or anxiety measured at a subsequent time point. Where the estimation of a risk ratio is not possible (refer to Figure 2), for example, where the total number of people exposed at baseline is not available (such as for retrospective or case-control studies) [29], odds ratios are estimated using standard logistic regression techniques. Where only time-to-event data are available, hazard ratios are used, estimated by a Cox proportional hazards model. For rigor, all effect estimates will be accompanied by a 95% CI and exact *P* value [30].

Models can be fitted using any statistical analysis software, including R (R Core Team), SAS/STAT (SAS Institute Inc), Stata (StataCorp LLC), and SPSS (IBM Corp). Before fitting the relevant models, Member studies must assess model assumptions. Should any model assumptions be violated, an alternate approach to analysis may be selected. For example, the nonlinearity of continuous variables should be investigated, and transformations or nonlinear models fitted where necessary. Similarly, should any of the assumptions of Cox proportional hazards models be violated, alternative strategies will be deployed to account for these violations.

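### The missing-data fallback permits k-nearest-neighbor imputation under a self-contradictory condition and with no variance correction; used as single imputation, it can mislead the missing-data check

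*Protocol article*

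**What the plan says.** The Missing Data section, under Sensitivity Models, sets the order of work. First, "Each study initially uses a complete-case model, whereby individuals with missing observations are excluded from the model". Then "Member Studies with missing exposure, outcome, and covariate observations" are to "conduct a missing data analysis to determine the influence of missing data". On method it says "While a multiple imputation approach is preferred", and continues that "other methods such as k-nearest neighbor imputation or inverse probability weighting may be used where an imputation approach is not possible or appropriate". It gives no number of neighbors, no matching variables, no repeated draws and no variance rule for kNN.

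Two other places fix what a study must deliver. A footnote to Table 1 says "Analyses using continuous exposures are required by the GLAD Taskforce". The section on estimating ratios says "Each study is required to use risk ratios (estimated by Poisson regression with robust SE) as the primary means", and that "all effect estimates will be accompanied by a 95% CI and exact" P value. The slope and its SE are therefore the products of every model. The Results section describes the text of this paper as the statistical analysis plan that member studies are to follow.

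**The concern.** There are two faults, one of wording and one of statistics.

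**Wording.** kNN is called imputation in the same sentence that offers it for the case where imputation cannot be used. Of the two fallbacks named, only inverse probability weighting meets the stated condition.

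**Statistics.** The sentence sets kNN against multiple imputation, so the natural reading is that each gap is filled once. The filled values are then analyzed as if observed, and nothing in the plan corrects the SE. If the fill is an average over several neighbors, the filled exposures also vary too little, which distorts the slope.

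At stake is the one analysis meant to show whether missing data influence the result. If the imputation itself moves the estimate or narrows its interval, a study may report missing-data bias where there is none. The 18 listed cohorts would each apply this permission on their own, and a single-kNN analysis would count as following the plan.

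**Working it through.** **No figure to reproduce.** The article gives no missing-data rate, effect size or incidence for this point. All simulation inputs are assumptions and the sizes are illustrative.

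**Main simulation.** From the article: Poisson regression with robust SE, a continuous exposure, and adjustment for age, sex and socioeconomic status. Assumed: true RR 0.85 per SD of exposure (log RR = ln 0.85 = -0.1625), incidence about 12%, missingness dependent on covariates, 10% or 30% missing, n = 1,500 or 6,000, 400 replicates per scenario. The SE ratio is the mean reported SE divided by the empirical SD of the estimates; 1 is correct.

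Exposure 30% missing (n = 1,500 / n = 6,000):

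| Method | Mean RR | SE ratio | 95% CI coverage |
|---|---|---|---|
| Complete case | 0.852 / 0.848 | 0.98 / 1.03 | 92.7% / 97.0% |
| kNN, k=5, outcome matched | 0.807 / 0.800 | 0.67 / 0.71 | 77.0% / 62.5% |
| kNN, k=5, outcome not matched | 0.863 / 0.862 | 0.98 / 1.02 | 94.3% / 95.0% |
| kNN, k=1, outcome matched | 0.850 / 0.848 | 0.69 / 0.74 | 81.2% / 85.5% |
| Multiple imputation, Rubin's rules | 0.853 / 0.849 | 0.97 / 1.00 | 93.8% / 94.8% |
| Inverse probability weighting | 0.851 / 0.848 | 0.97 / 1.03 | 92.2% / 96.3% |

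**Slope.**
- k=5, outcome matched: mean log RR -0.2141 and -0.2228. Dividing by -0.1625 gives 1.32 and 1.37, so 32% and 37% too large.
- k=5, outcome not matched: -0.1469 and -0.1482, ratios 0.90 and 0.91, so 9% to 10% attenuated.
- k=1: no material bias.

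**Hand check of the slope.** Let f be the missing share, and scale the exposure variance left after the covariates to 1. A mean of k donors has variance about 1/k, so the completed exposure has variance (1 - f) + f/k. For f = 0.3 and k = 5 this is 0.7 + 0.06 = 0.76.
- Matching on the outcome roughly keeps the covariance with the outcome, so the slope is multiplied by about 1/0.76 = 1.32.
- Matching without it keeps only the observed part, so the slope is multiplied by about 0.7/0.76 = 0.92.
- With k = 1 the variance is 1 and the first factor is 1.

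This approximation agrees with the simulation in direction and rough size, and it does not depend on the assumed RR.

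**SE.** With k=1 and n = 1,500, the mean reported SE was 0.0729, the same as with no data missing (0.0729). The true spread was 0.1056, wider than complete case (0.0913). The filled values are counted as information that is not there.

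**Outcome 30% missing.**
- k=5 matched on the exposure: RR 0.835 / 0.834, SE ratio 0.81 / 0.78, coverage 88.2% / 86.0%.
- k=5 not matched on the exposure: RR 0.862 / 0.862, SE ratio 0.97 / 0.92, coverage 93.2% / 90.7%.
- k=1: RR 0.851 / 0.853, SE ratio 0.74 / 0.68, coverage 85.3% / 82.0%.

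**10% missing.** Coverage was 88% to 93% for k=1 and for k=5 when the exposure or outcome (whichever was not missing) was a matching variable, and 94% to 96% for k=5 without it.

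**Two further simulations**, both with n = 2,000 and exposure missing completely at random:
- 30% missing: k=5 matched on the outcome overstated the log RR by about 27%, SE ratio 0.61, coverage 75%; k=1 was unbiased, SE ratio 0.72, coverage 80%.
- True log RR -0.15, k=5 matched on the outcome: at 20% missing, mean -0.17 and coverage 86%; at 40% missing, mean -0.21, reported SE 0.076 against a true 0.120 (ratio 0.63), coverage 74%. Complete case covered 95% in both.

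**The case against.** **The contradiction is probably a slip.** The only imputation approach named before the clause is multiple imputation, so the intended condition is very likely that multiple imputation cannot be used. This stands, and it settles the wording. It does not settle the statistics: the repaired sentence would still permit kNN as something other than multiple imputation.

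**The article does not say that kNN is used as single imputation.** Donors can be drawn repeatedly or the whole procedure bootstrapped, and the references cited there may cover this. It stands that single imputation is an inference. It is the natural one, because kNN is contrasted with multiple imputation and no combining or variance rule is given.

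**The faults are not universal.** A reader might infer that single kNN always gives intervals that are too narrow and a biased slope together. The results do not support that. At 30% missing exposure, k=1 was nearly unbiased but too narrow, and k=5 without the outcome was attenuated with about correct SEs. Both faults came together when k=5 was matched on the outcome. This stands in full and limits the claim.

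**The simulations do not cover the hardest case.** Missingness was completely at random or depended only on adjusted covariates, so complete case was valid throughout. No run shows how kNN behaves where complete case is biased. This also stands. The runs do show that kNN can create a discrepancy where none exists.

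**The reach is small.** kNN is one optional example within a sensitivity analysis, and no member study is said to use it. This stands and bears on the weight of the point.

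**Conclusion.** The point holds in limited form. The condition is contradictory as worded, and the underlying permission lets a study report a missing-data analysis with no correction for imputation uncertainty. Used as single imputation with the outcome among the matching variables, and with 30% of the exposure missing, kNN gave SEs about 0.6 to 0.75 of the true value and coverage of about 63% to 86%. Neighbor averaging biased the slope in either direction, depending on whether the outcome was matched. Effects were smaller at 10% missing. Every size rests on assumed incidence, effect, missing share and kNN settings; the article supplies none of these and nothing that would steer a study to a safer variant.

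A reader might also infer that the main or pooled results are compromised. The article does not support that. The initial model is complete case, and nothing says that imputed estimates will be pooled; the meta-analysis is to have its own protocol. The damage is confined to the check on missing data. That is still worth correcting, because in these settings the permitted method performed worse than the complete-case result it was meant to test, while multiple imputation and weighting kept coverage at 92% to 96%.

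**What to change.** Replace the fallback clause with wording such as: *If multiple imputation cannot be carried out or is unsuitable, inverse probability weighting with robust SE may be used. Nearest-neighbor donors may be used only within multiple imputation (predictive mean matching, combined by Rubin's rules, with the outcome and all model covariates in the imputation model) or with a bootstrap that repeats the imputation in each resample.*

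This removes the contradiction and the uncorrected single-imputation route while keeping neighbor donors available in a sound form. It changes one sentence of the plan. The cost is slightly more analysis work for any study that would have used single kNN; the complete-case models are untouched.

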### Future Directions: Meta-Analyses

Upon completion of the analysis phase of the GLAD project (phase 2), the GLAD project team and advisory group will lead a meta-analysis (phase 3). A separate protocol will be created for this phase of the GLAD project. Briefly, the GLAD project team will conduct a systematic literature review to identify any relevant studies not already participating in GLAD. After screening abstracts and full text, data will be extracted from all identified studies and studies participating in GLAD. A random effects meta-analysis will be performed to pool results from all eligible studies. We will perform a meta-regression to quantify how the risk can vary by demographic factors, and methodological biases [42]. Where studies have used different assessment methods for mental health outcomes, different tools to ascertain dietary intake, any slight deviations to definitions, or where studies use different analysis strategies, we will perform cross-walking or sensitivity analyses to ensure comparability [43]. Papers using methods that deviate substantially from the methods described in this paper will be excluded from the meta-analysis. The resulting meta-analysis will be reported according to the PRISMA (Preferred Reporting Items for Systematic Reviews and Meta-Analyses).

### Ethical Considerations

Each member study will have obtained informed consent from participants and had their study approved by institutional ethics review boards. Full details for ethics for each study can be found in previous studies [44-65] and a summary is provided below. This study is registered in the Open Science Framework (osf.io/zbg6x).

## Results

As of August 2024, 18 longitudinal studies have agreed to participate in the GLAD project (Table 3). These studies have sample sizes ranging from 639 participants to 171,000 participants (Table 4).

The GLAD project comprises 3 essential phases, which will be repeated for other lifestyle exposures of interest: (1) conducting a systematic search to identify relevant studies and recruit study leads to contribute data, (2) generating estimates of study-level associations of dietary risk factors with CMDs using harmonized data analysis protocols developed by the GLAD Taskforce and approved by the GBD, and (3) pooling results from each study to provide the GBD with robust estimates to calculate the diet-CMD risk-outcome pairs in the first instance.

As of August 2024, phase 1 of the GLAD project has been completed, and phase 2 is due for completion in early 2025, at which time phase 3 of the GLAD project is due to begin (Figure 3).

Phase 1 includes searching for and recruiting studies with suitable data, harmonizing data definitions by ensuring member studies use the exposure definitions listed in Table 1 and the outcome definitions listed in Table 2, and harmonizing data analyses by ensuring member studies follow the statistical analysis plan presented in this paper.

**Table 3 table3:** Details of the ethics approval for currently listed member studies^a^.

Study name	Ethics review board
The African-PREDICT^b^ study [44]	North West Department of Health and Health Research Ethics Committee of the North-West University.
Child to Adult Transition Study [45]	Royal Children’s Hospital Human Research Ethics Committee.
Dunedin Study [46]	Health and Disability Ethics Committee, Ministry of Health.
Environmental Risk (E-Risk) Longitudinal Twin Study [47,48]	Joint South London and Maudsley and the Institute of Psychiatry Research Ethics Committee.
Fragility in the Elderly Lombardy Study [49]	Ethics committee of the University of Pavia.
Geelong Osteoporosis Study [50]	Barwon Health Human Research Ethics Committee.
Health4Life [51,52]	University of Sydney, NSW^c^ Department of Education, University of Queensland, Curtin University, and relevant Catholic school ethics committees.
Healthy Life in an Urban Setting [53]	Ethical Review Board of the Academic Medical Center Amsterdam.
Longitudinal Aging Study Amsterdam [54]	Medical ethics committee of the VU University Medical Center.
Lothian Birth Cohort 1936 [55,56]	Multi-Centre Research Ethics Committee for Scotland and Lothian Research Ethics Committee.
Melbourne Collaborative Cohort Study [57]	Cancer Council Victoria's Human Research Ethics Committee.
Moli-sani Study [58]	Ethical committee of the Catholic University in Rome.
Netherlands Study of Depression and Anxiety [59]	Medical Ethical Committee of the Vrije Universiteit (VU) Medical Centre and medical ethical committees of the participating universities.
Northern Ireland Cohort of Longitudinal Ageing [60]	School of Medicine, Dentistry and Biomedical Sciences of Queen’s University Belfast.
NutriNet Brasil [61]	Ethics committee of the School of Public Health from São Paulo University
NutriNet-Santé [62]	Ethics committee of the French National Institute for Health and Medical Research and by the National Commission on Informatics and Liberty.
Piccolipiù/Piccoli+/Piccolipiù in Forma [63]	Ethics committees of the Local Health Unit Roma E (management center), of the Istituto Superiore di Sanità (National Institute of Public Health) and of each local center.
REgistre GIroní del COR [64,65]	Institut Municipal d'Assistencia Sanitaria Ethics Committee

^a^Additional studies may be participating in or providing data for the GLAD project and not be listed here.

^b^African-PREDICT: African Prospective study on the Early Detection and Identification of Cardiovascular disease and Hypertension.

^c^NSW: New South Wales.

**Table 4 table4:** Overview of the studies participating in the GLAD^a^ project.

Study name	Study location	Maximum possible sample size^b^, n	Age range
The African-PREDICT^c^ Study [44]	South Africa	1202	20-30 years
Child to Adult Transition Study [45]	Australia	1239	Older than 8 years
Dunedin Study [46]	New Zealand	1037	0-45 years
Environmental Risk (E-Risk) Longitudinal Twin Study [47,48]	United Kingdom	2232	0-18 years
Fragility in the Elderly Lombardy Study [49]	Italy	639	Older than 65 years
Geelong Osteoporosis Study [50]	Australia	1518	Older than 30 years
Health4Life [51,52]	Australia	6639	11-13 years; 14-17 years
Healthy Life in an Urban Setting [53]	The Netherlands	24,789	18-70
Longitudinal Aging Study Amsterdam [54]	The Netherlands	3805	55-85 years
Lothian Birth Cohort 1936 [55,56]	United Kingdom	1091	Older than 60 years
Melbourne Collaborative Cohort Study [57]	Australia	41,500	Older than 40 years
Moli-sani Study [58]	Italy	24,325	Older than 35 years
Netherlands Study of Depression and Anxiety [59]	The Netherlands	3348	18-65 years
Northern Ireland Cohort of Longitudinal Ageing [60]	United Kingdom	8500	Older than 50 years
NutriNet Brasil [61]	Brazil	109,245	Older than 18 years
NutriNet-Santé [62]	France	171,000	Older than 18 years
Piccolipiù/Piccoli+/Piccolipiù in Forma [63]	Italy	3328	0-4 years
REgistre GIroní del COR [64,65]	Spain	11,158	Older than 26 years

^a^GLAD: Global burden of disease Lifestyle And mental Disorders.

^b^Maximum possible sample size refers to the largest reported sample size from study publications, study websites study protocol, or profile papers. The actual sample size to be included in the GLAD project may vary.

^c^African-PREDICT: African Prospective study on the Early Detection and Identification of Cardiovascular disease and Hypertension.

**Figure 3 figure3:**
[figure not shown]
The tasks, responsible parties, phases, and expected timeline of the GLAD project. CMD: common mental disorder; GBD: Global Burden of Diseases, Injuries, and Risk Factors Study; GLAD: Global burden of disease Lifestyle And mental Disorders.

## Discussion

### Anticipated Impact

The GLAD project is a global collaboration designed to estimate the risk of CMDs attributable to lifestyle risk factors, with this protocol focusing on dietary risk factors. The anticipated results will provide the GBD with the required threshold of evidence for lifestyle risks to be causally related to CMDs, thereby enabling lifestyle-CMDs risk-outcome pairs to be integrated into the GBD framework. Specifically, the GLAD project will demonstrate that GBD-defined lifestyle risks (eg, diets low in fruit) will be associated with increased risk of CMDs. The GBD study is the largest and most comprehensive global epidemiological health study, providing metrics for 369 diseases and injuries and 87 risk factors [19,66]. These health metrics, including estimates such as the burden of disease and disability-adjusted life years, are publicly available via the GBD digital platform [13] and provide critical information for clinicians, researchers, and policy makers worldwide. While lifestyle risk factors, including dietary intake defined as per GBD-specific definitions, have been considered in the context of chronic physical conditions in the GBD study, they have not yet been linked with mental health outcomes. As the first global collaborative study to link these lifestyle risks with CMDs, using the definitions and methods concordant with the GBD, the results of the GLAD project can be used to link these lifestyle factors as risks for CMDs in the GBD. This effort will allow us to quantify the potential reduction or elimination of the CMD burden by targeting these risk factors at regional and global levels, and to ensure these data are available freely online via the GBD VizHub Data visualization tool.

Risk factors for CMDs in the GBD are currently limited, and so, the inclusion of these additional lifestyle risk factors will represent a significant expansion in the scope of the GBD, which will have global policy implications. Our work builds upon the previous efforts of studies that have successfully integrated novel risk factors for CMDs in the GBD. For example, bullying victimization has been successfully incorporated into the GBD as a level 3 risk and is now routinely integrated into GBD papers [67,68]. By emulating the successful integration of these other risk factors into the GBD, our comprehensive, collaborative approach to harmonized statistical analyses across multiple, internationally renowned epidemiological cohorts has the potential to establish a basis for evidence-backed preventive strategies focused on lifestyle risk factors to reduce the burden of CMDs. Furthermore, by operationalizing the definitions to be in line with the GBD, which are used to inform global policy guidelines, and by capturing data from different regions, sexes, and ages, these results have the potential to bring benefits to individuals and communities on a global scale.

There is substantial observational [69-71], intervention [72-76], and meta-analytical [5,77-79] evidence linking these lifestyle factors to CMDs globally, which suggests that lifestyle factors are potentially suitable (and importantly, modifiable) preventive strategies. This has been recognized by the Royal Australian and New Zealand College of Psychiatrists, with lifestyle treatments integrated into the recent clinical practice guidelines for mood disorders, including depressive disorders [9]. A 2020 meta-review identified that targeting lifestyle variables like physical activity and smoking can be used effectively in the prevention and treatment of CMDs [5]. However, there was less evidence for the role of targeting diet in preventing CMDs, particularly as defined by international policy guidelines or as per the GBD framework. In order to incorporate additional lifestyle factors into guidelines globally, we need comprehensive epidemiological evidence, with a particular focus on dietary risks. The GLAD project will address previous methodological limitations through global collaborations and following a rigorous methodological framework informed by the GBD.

Although mechanistic evidence is currently limited, the causal role of lifestyle risks for CMDs has been supported by shared biological mechanisms between lifestyle factors and CMDs. These pathways include inflammation, oxidative stress, epigenetics, hypothalamic-pituitary-adrenal axis regulation, and the gut microbiome [80]. Inflammation has been linked to CMDs previously, and physical activity, diet, sleep, and smoking have all been shown to impact inflammation [5]. As such, improving dietary intake, increasing physical activity, improving sleep, and smoking cessation may improve mental health via anti-inflammatory properties. Another mechanistic pathway shared by CMDs and many lifestyle risk factors (including diet, physical activity, sleep, and smoking) is the microbiome [80,81]. Many of the dietary risks listed in the GBD, including fruit, vegetable, whole grain, and fiber intake, have pre- and probiotic potential which has been shown to beneficially influence the gut microbiome, and other GBD-defined dietary risks, such as processed meats and sugar-sweetened beverages (which are markers for a high-fat diet), Western-style diet (have been shown to increase anxiety and depression via gut microbiome alterations) [80]. Despite the evidence linking lifestyle risk factors with CMDs, including studies identifying potential mechanisms of action, studies assessing the relationship between lifestyle risks as defined by the GBD with CMD outcomes are lacking. Further, to integrate lifestyle risks for CMDs in the GBD, evidence needs to be generated globally, and not just from individual studies. As a global collaborative project, the results from the GLAD project will therefore provide the necessary evidence to incorporate lifestyle as a risk factor for CMDs in the GBD, which will enable policy makers around the world to make policy decisions regarding the potential public health benefit of population-level lifestyle improvements to mental health.

